#### Basic Clinical Data Collection

The following data will be collected: (1) clinical basic characteristics including sex, gestational age, birth weight, delivery mode, Apgar score at 1, 5, 10 min; (2) characteristics of cord blood processing including cord blood volume, cell number, cell concentration before and after processing, CFU-GM, CD34+ cell count, cell viability post processing; (3) characteristics of infusion cells including total cell number, time between collection (birth) and initiation of infusion, infused volume, and pathogen detection (including bacteria culture, fungus culture, HIV, HBV, HCV, CMW, and *Treponema pallidum*) results; and (4) other routine clinical interventions including dose and times of pulmonary surfactant (PS) replacement, postnatal steroid use, surgical closure of patent ductus arteriosus, and use of blood products.

We will use the following clinical definitions in this study:

Gestational age will be determined on the basis of a combination of the last menstrual period and early ultrasound findingsThe diagnosis of common preterm complications will include the following (23):

BPD, defined as treatment with oxygen >21% for at least 28 days, and its severity will be assessed at 36 weeks of postmenstrual age or discharge home whichever comes first. Mild BPD, defined as breathing room air at assessment. Moderate BPD, defined as the need for <30% supplemental oxygen, and severe BPD defined as needing ≥30% supplemental oxygen or positive airway pressure. For these patients, BPD status will be analyzed by a committee of three independent experts blinded to the study group.

RDS will be defined if the infants show evidence of respiratory symptoms such as grunting and chest retraction, typical chest radiograph findings, and/or treatment with surfactant, and the need for assisted ventilation.

NEC will be defined using Bell's classification. Infants with stage II or above will be diagnosed with NEC.

LOS will be defined if the infants had a positive bacterial culture results after the first 72 h after birth.

ROP will be defined according to the International Classification for Retinopathy of Prematurity.

Anemia will be defined as hemoglobin no more than 140 g/L.

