#### Follow Up

All the infants will be followed until the corrected age of 2 years old, the following parameters will be recorded.

- Anthropometric characteristics: weight, length, and head circumference.- Respiratory outcomes including the occurrence of wheezing, asthma, nocturnal cough, supplemental oxygen requirement, and rehospitalization because of pneumonia.- Degree of neurodevelopmental impairment via standardized neurological examination [using the revised Brunet-Lézine [RBL] global developmental quotient score (16)], and other major neurodevelopmental outcomes including cerebral palsy, seizures, auditory impairment, and visual impairment (Table 2).

**Table 2 T2:** Contents and points of data capture: Standard Protocol Items: Recommendations for Interventional Trials (SPIRIT) schedule of enrolment, interventions, and assessments.

**Visit**	**Screening**	**Intervention**	**Follow up**	
	**V1**	**V2**	**V3**	**V4**
Time point	born	Within 24 h after birth	36 weeks of postmenstrual age	Corrected age of 2 years old
Informed consent form	√			
Screening the subject	√			
Demographic information	√			
Inclusion/exclusion criteria	√			
Get random number	√			
Cord blood process		√		
Vital signs	√	√	√	
Chest radiographs		√		
Pulmonary surfactant replacement		√		
Mechanical ventilation	√	√		
Arterial blood oxygen saturation	√	√		
Laboratory tests	√	√	√	
Blood routine test	√	√		
Blood gas	√	√		
Safety outcomes		√	√	√
Record adverse events		√	√	√
Postnatal steroid use		√	√	√
Surgical closure of patent ductus arteriosus		√	√	
Blood products use		√	√	
Bronchopulmonary dysplasia			√	
Other preterm complications			√	
Duration of hospitalization			√	√
Anthropometric Characteristics			√	√
Respiratory Outcomes				√
Neurodevelopmental outcomes				√

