### Statistical Analysis

Statistical analyses between the two groups will be performed using an unpaired two-tailed Student's *t*-test or Chi-squared Test as appropriate. A logistic regression model will be used for the entire study population (i.e., without removing deaths) to adjust for the effect of treatment on primary outcome according to baseline characteristics and events known to affect the occurrence of BPD (i.e., gestational age, birth weight and other characters that are different in two groups after initial analysis), and to investigate the effect of treatment on the following outcomes: extubation rates, severe adverse events, and death before discharge. The Breslow-Day test and Corchran-Mental-Haenszel (CMH) test will be used to adjust the data derived from different participating centers. The results will be reported as odds ratio (OR) with 95% confidence intervals (CI). All statistical tests will be two-tailed and a *p* < 0.05 will be considered statistically significant. All statistical analysis will be performed using SPSS 21.0 (IBM).

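### The continuous 2-year outcomes fall to an unadjusted t-test although gestational age and birth weight are collected: valid, but an avoidable loss of precision whose size the documents do not fix

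*Protocol article*

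**What the plan says.** All references are to the protocol article.

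- **General method (Statistical Analysis).** "Statistical analyses between the two groups will be performed using an unpaired two-tailed Student's" t-test, with the chi-squared test as the alternative where appropriate. No other method for a continuous outcome appears.
- **Adjusted model (Statistical Analysis).** A logistic regression is planned "to adjust for the effect of treatment on primary outcome according to baseline characteristics and events known to affect the occurrence of BPD". Its covariates are "gestational age, birth weight and other characters that are different in two groups after initial analysis". It also covers "the following outcomes: extubation rates, severe adverse events, and death before discharge". No 2-year outcome is named.
- **Centre (Statistical Analysis).** The Breslow-Day and CMH tests "will be used to adjust the data derived from different participating centers". These are methods for categorical data. The effect measure to be reported is the odds ratio.
- **2-year outcomes (Follow Up).** "Anthropometric characteristics: weight, length, and head circumference", and the "revised Brunet-Lézine [RBL] global developmental quotient score". Secondary Objectives, item 6, makes the long-term outcomes a secondary objective.
- **Baseline data (Basic Clinical Data Collection).** "clinical basic characteristics including sex, gestational age, birth weight, delivery mode, Apgar score at 1, 5, 10 min".

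**The concern.** The plan treats gestational age and birth weight as prognostic, since it adjusts the primary outcome for them. It does not use them for the continuous outcomes at 2 years. Any variance in growth or developmental quotient that they explain stays in the error term of the t-test, and the confidence interval is wider than it need be.

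These are also the outcomes assessed in the fewest infants, after deaths and a loss to follow-up that the Sample Size section puts as high as 20%. What is at stake is the precision of secondary evidence on long-term benefit and safety. The primary analysis is not affected.

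**Working it through.** **The plan's own figure.** The documents give no sample-size or power figure for the 2-year outcomes. The one stated figure, for BPD, reproduces. With pA = 0.60, pB = 0.35, two-sided 5%, 80% power and κ = 1:

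n = (0.60 × 0.40 + 0.35 × 0.65) × ((1.960 + 0.842) / 0.25)² = 0.4675 × 125.6 = 58.7, so 59 per group as stated.

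**Inputs for the 2-year outcomes**

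- Enrolment of 200 at 1:1 (Study Design and Settings).
- Loss of 20% (Sample Size), leaving 160 infants, 80 per arm. Deaths are ignored, so this is an upper figure.
- Two-sided 5% (Statistical Analysis).
- R2, the share of outcome variance explained by gestational age and birth weight. This is not in the documents. It is assumed and varied from 0.01 to 0.25.

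**Reference difference.** The t-test has 80% power at (1.960 + 0.842) × √(2/80) = 0.443 SD.

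**Effect of adjustment.** A linear model reduces the residual SD by the factor √(1 − R2). Power at the reference difference is Φ(2.802/√(1 − R2) − 1.960). For R2 = 0.09 this is Φ(2.802/0.954 − 1.960) = Φ(0.977) = 83.6%. The detectable difference is 0.443 × √(1 − R2), and the 160 infants count as 160/(1 − R2) under the t-test. To allow for two covariates, the fifth column multiplies the SD by √(157/155) = 1.006.

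| R2 | SE falls by | Detectable at 80% power (SD) | Power at 0.443 SD | Same, after cost of 2 df | Equivalent infants |
|---|---|---|---|---|---|
| 0.01 | 0.5% | 0.441 | 80.4% | 79.9% | 162 |
| 0.04 | 2.0% | 0.434 | 81.6% | 81.1% | 167 |
| 0.09 | 4.6% | 0.423 | 83.6% | 83.1% | 176 |
| 0.16 | 8.3% | 0.406 | 86.4% | 85.9% | 190 |
| 0.25 | 13.4% | 0.384 | 89.9% | 89.5% | 213 |

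**Sensitivity to the total.** The Sample Size section arrives at 140, not 200. Less 20%, that is 112 infants, 56 per arm, and the reference difference becomes 2.802 × √(2/56) = 0.529 SD. Power before the degrees-of-freedom cost is unchanged, because the number of infants cancels from the formula once the difference is set where the t-test has 80% power.

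**The case against.** **Nothing is stated wrongly.** Under randomisation the unadjusted t-test is valid, and its standard error already allows for chance imbalance in gestational age. This stands. A reader might infer that the 2-year comparisons would be biased because imbalance goes uncorrected. The documents do not support that; the loss is one of efficiency.

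**Covariates for secondary endpoints belong in a SAP that is not shown.** This would answer a complaint about missing detail. Here the protocol does fix a test for continuous data and fixes where adjustment applies, and the point concerns that stated choice.

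**The link to the 2-year outcomes is inferred.** Statistical Analysis does not name them, Outcome Measures does not list them, and the developmental quotient might be analysed in categories of impairment. This stands in part. The link follows because no other method for continuous data is given, and item 6 of the secondary objectives includes these outcomes. If the quotient is categorised, the point covers only the three growth measures.

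**The gain may be negligible.** This stands. All infants are under 28 weeks, which narrows gestational age, and birth weight is correlated with it. A reader might start at R2 = 0.10 to 0.30 and take a 0.5 SD difference, for which power rises from 75% to 80–89% at 56 per arm, or from 88% to 92–97% at 80 per arm. That arithmetic is right, but neither the R2 range nor the 0.5 SD comes from the documents, and the range omits the low end where the gain disappears.

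**Sex can be counted twice.** If growth is expressed as sex-standardised scores, most of the variance due to sex is already removed, and adding sex as a covariate buys little. This also stands.

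**Conclusion.** The point holds as a modest improvement for continuous 2-year secondary outcomes. The plan's only stated method for them ignores two prognostic covariates that it collects and uses elsewhere. At the difference the t-test detects with 80% power, adjustment gives anything from no gain (R2 = 0.01) to about 90% power (R2 = 0.25). This assumes 160 infants assessed, no allowance for deaths, and a linear relation with the covariates. Neither the t-test nor the linear model deals with deaths or missing visits.

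A reader might extend the argument to the binary secondary outcomes left to the chi-squared test, such as NEC or PVL. That does not follow. Logistic adjustment targets a conditional odds ratio, generally does not shrink the standard error of the log odds ratio, and with several covariates may be unstable for uncommon complications in 140 to 200 infants. The chi-squared test is defensible there.

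**What to change.** For 2-year weight, length, head circumference and developmental quotient, pre-specify as the main analysis a linear regression on treatment, gestational age and birth weight. Add sex only where the outcome is not already sex-standardised. Report the adjusted mean difference with its 95% CI, and keep the t-test as a supportive analysis.

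Fix the covariates in advance. The rule in the logistic model that adds characteristics found to differ between the groups should not be carried over.

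Leave the chi-squared tests for the remaining binary secondary outcomes as they are.

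The cost is a change of wording before unblinding and two or three degrees of freedom. The covariates are already collected, and the stated software fits the model.

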With these concepts in mind, the authors have tried to clarify the effects of ACBMNC cell infusion for the prevention of BPD since 2009. In the first study performed at our hospital, the safety and feasibility of ACBMNC infusion in preterm infants was demonstrated (9). Subsequently, we compared the effectiveness of ACBMNC infusion in those patients at our center (8). We found that ACBMNC infusion resulted in a significant decrease in the duration of mechanical ventilation (3.2 vs. 6.41 days, *p* = 0.028) and in the need for oxygen therapy (5.33 vs. 11.31 days, *p* = 0.047) (8). Given the small sample size and comparatively high gestational age of the enrolled preterm infants, no statistically significant differences in BPD incidence were observed in the previous small-sample trial. Therefore, our aim is to conduct a large-scale, multi-center, blinded randomized clinical trial (RCT) to evaluate the efficacy of ACBMNC infusion in BPD prevention in extremely preterm neonates.

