#### Randomization

The randomization sequence will be generated electronically using SPSS (version 21). Following enrolment, treatment will be assigned after verification of eligibility and consent status. Computer generated randomization will be performed by the statistician in our center at a 1:1 ratio. A randomization number will be assigned by computer for each enrolled infant. Infants will be randomized to the order in which they receive ACBMNC and placebo infusions. Those enrolled in the ACBMNC group will receive an infusion of ACBMNC within 24 h after birth. Those in the placebo group will receive an infusion of a placebo solution, consisting of normal saline with the same volume. Cell dose for all patients to be targeted at 5 × 10^7^ cells per kilogram.

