### Outcome Measures

*Primary outcome measure:*

- The frequency of BPD or death in at 36 weeks of postmenstrual age or discharge home whichever comes first.

*Secondary outcome measures:*

- Mortality rate- Incidence of BPD- Incidence of other preterm complications including IVH, PVL, NEC, ROP, RDS, VAP, LOS, and anemia [all clinical diagnoses will be defined according to a standard references (16)].- Duration of hospitalization.- Duration of mechanical ventilation and oxygen therapy- Frequency of re-intubation.- The time (days) return to BW.

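### The covariate rule for the adjusted primary-outcome model is not limited to pre-infusion variables and selects on observed differences between arms, so it permits adjustment for consequences of treatment

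*Protocol article*

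**What the plan says.** The primary outcome (Outcome Measures) is "The frequency of BPD or death in at 36 weeks of postmenstrual age or discharge home whichever comes first". For it, the Statistical Analysis section of the protocol article plans this: "A logistic regression model will be used for the entire study population (i.e., without removing deaths"). The model adjusts the treatment effect for "baseline characteristics and events known to affect the occurrence of BPD". A bracket opening with 'i.e.' lists the adjusters as "gestational age, birth weight and other characters that are different in two groups after initial analysis".

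The same section also plans an unadjusted t-test or chi-squared test as appropriate, and Breslow-Day and Cochran-Mantel-Haenszel (CMH) tests to account for centre. It does not say which result is primary.

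Three other places bear on the reading:

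- **Randomization:** "Those enrolled in the ACBMNC group will receive an infusion of ACBMNC within 24 h after birth". Most of the hospital course therefore follows treatment.
- **Basic Clinical Data Collection:** alongside sex, gestational age and Apgar score, item 4 lists surfactant doses, "postnatal steroid use, surgical closure of patent ductus arteriosus, and use of blood products". Table 2 records steroids, ductus surgery and blood products at the 36-week visit as well as at the infusion visit.
- **Background:** in the sponsor's earlier study "ACBMNC infusion resulted in a significant decrease in the duration of mechanical ventilation" (3.2 v 6.41 days), and oxygen therapy was also shorter (5.33 v 11.31 days).

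**The concern.** The rule has two weaknesses.

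1. It places events beside baseline characteristics and sets no time limit on either the events or the further characters.
2. It chooses the further covariates by comparing the arms once the data are in.

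The two reinforce each other. Under randomisation a true baseline variable differs between arms only by chance, whereas a variable that treatment changes differs systematically. Selection on observed difference therefore favours variables affected by treatment, if any are eligible.

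Conditioning on such a variable removes the part of the effect that passes through it. It can also add bias where unmeasured severity drives both the event and the outcome. The adjusted odds ratio would then no longer estimate the effect of assignment to the infusion. Oxygen duration shows this most plainly: the protocol's definition of BPD begins with at least 28 days of oxygen, so adjusting for it comes close to adjusting for the outcome itself.

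**Working it through.** **The plan's own figure.** Inputs from Sample Size: 60% v 35%, with the stated 80% read as power and the 5% as two-sided alpha (their symbols are interchanged in the text). With equal arms the plan's formula gives

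n = (0.60×0.40 + 0.35×0.65) × ((1.960 + 0.842)/0.25)² = 0.4675 × 125.6 = 58.7, rounded up to 59 per group, as stated.

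Unadjusted power at these rates is about 95% at 100 per arm (the 200 in Study Design and Settings) and about 85% at 70 per arm (the 140 in Sample Size). The planned odds ratio is (0.35/0.65)/(0.60/0.40) = 0.36. These are BPD rates, used here as a stand-in for BPD or death.

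**What one post-infusion event does to the odds ratio.** The documents give no event rates, so these are assumed: event in 50% of controls and 30% of treated infants, with an odds ratio of 4 for the outcome. Let x be the outcome odds without the event. The arm totals are kept at 60% and 35%.

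- Control: 0.5·4x/(1+4x) + 0.5·x/(1+x) = 0.60, so 3.2x² − x − 1.2 = 0 and x = 0.788.
- Treated: 0.3·4x/(1+4x) + 0.7·x/(1+x) = 0.35, so 2.6x² + 0.15x − 0.35 = 0 and x = 0.339.
- Odds ratio with the event in the model: 0.339/0.788 = 0.43, against 0.36 without it.

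**What the selection rule does to power.** Simulated trials (4,000 per scenario, except the milder event at 2,000) added the event only when it differed between arms at p<0.05. That threshold is an assumption, because the plan does not say how a difference is judged. Gestational age and birth weight were not in the model.

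| Assumed event | Per arm | Event selected | Power without event | Power under the rule |
|---|---|---|---|---|
| 50% v 30%, OR 4–6 | 100 | 83–84% | about 95% | about 75–80% |
| 50% v 30%, OR 4–6 | 70 | 67–68% | about 85% | about 62–67% |
| 50% v 40%, OR 3 | 100 | – | about 95% | about 93% |

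In the first row the average odds ratio is 0.42–0.44.

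**A second set-up.** Here the event is always in the model and carries a stated share of the 25-point effect (assumed event rates 60–70% control, 25–35% treated, 100 per arm). With a quarter of the effect carried, the odds ratio is 0.45–0.46 and power 69–74%. With half carried, they are 0.54–0.57 and 41–47%. The direction is the same, and the size follows the assumption.

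**Baseline-only reading.** If K independent, truly balanced baseline variables are each screened at p<0.05, the chance of selecting at least one is 1 − 0.95^K. That is 23% for K = 5, 40% for K = 10 and 54% for K = 15. The covariate set would then be decided by chance imbalance after the data are seen.

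**The case against.** The strongest reply is that the bracket defines the adjusters. Both covariates it names are fixed at birth, no post-infusion variable is named, and 'characters' may simply mean baseline characteristics. Basic Clinical Data Collection uses 'characteristics' for items 1 to 3 and a different label for the later interventions in item 4, and nothing expressly links item 4 to the model. This reading is open, so the harm cannot be called certain. It does not clear the text, however: events are listed in addition to baseline characteristics, and selection after an initial analysis remains on either reading.

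Second, the chi-squared and CMH analyses do not use this covariate rule, and the unadjusted test keeps its error rate and power. That stands. A reader might infer that the trial's main result will be adjusted away, but the documents do not make the adjusted model decisive. Nor do they make any other analysis decisive.

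Third, a reader might infer that steroids, ductus surgery, transfusion and surfactant are all on the path from infusion to BPD. Background supports an effect only on ventilation and oxygen duration. Surfactant is described as routine and appears in Table 2 only at the visit within 24 h of birth, so it may precede the infusion.

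Fourth, a reader might extend the rule to death before discharge and severe adverse events. The covariate clause is attached to the primary outcome. For the other outcomes the section says only that logistic regression will be used.

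Fifth, the simulations omit gestational age and birth weight, which the planned model always contains. With one prognostic baseline covariate added (assumed log odds ratio 0.8 per SD), power under the rule in the 50% v 30% scenario was about 85%, so the omission matters. A false signal is also possible (about 13–18% rejection at 100 per arm with no total effect), but that needs a direct harm exactly offsetting a mediated benefit, and little weight should rest on it.

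Finally, an unseen analysis plan may narrow the list. The point here is a rule the protocol states, not one it leaves out.

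**Conclusion.** The point holds as a defect of wording in the primary-outcome model. The rule leaves all covariates but two open, sets no pre-infusion limit, and selects on observed differences. It permits adjustment for consequences of treatment without requiring it. On the narrowest reading it is still data-driven covariate selection.

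No single figure for the loss can be taken from the documents. Under the assumptions shown, power at 100 per arm falls from about 95% to about 75–80% for a strong event (50% v 30%, OR 4–6) and to about 93% for a milder one (50% v 40%, OR 3), both without gestational age or birth weight in the model. These figures illustrate the mechanism and do not predict this trial's loss. The correction is worth making because it is nearly free and concerns an estimate of the primary treatment effect.

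**What to change.** In Statistical Analysis, delete 'and events' and the phrase admitting other characters that differ after initial analysis. State instead that the adjusted primary-outcome model uses a prespecified list of covariates fixed before infusion: gestational age and birth weight, plus any other pre-infusion factor named in advance. All are included whatever their observed balance.

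Report post-infusion events by arm. Keep any model that contains them as a labelled exploratory analysis; such analyses need not be barred. In the same edit, say which analysis of the primary outcome is primary.

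The cost is a sentence or two of protocol wording, repeated in the analysis plan. No new data are needed, since gestational age and birth weight are already collected. The change should be made before anyone sees outcome data by arm, because a covariate list settled afterwards cannot be shown to be independent of the results.

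### The covariate rule for the adjusted analysis of death or BPD is not limited to variables fixed before randomisation, so it permits adjustment for events that the infusion may have changed

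*Protocol article*

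**What the plan says.** The primary outcome (Outcome Measures) is "The frequency of BPD or death in at 36 weeks of postmenstrual age or discharge home whichever comes first". For this outcome the Statistical Analysis section plans a logistic model in the whole study population "to adjust for the effect of treatment on primary outcome according to baseline characteristics and events known to affect the occurrence of BPD". A bracket opened by i.e. then lists gestational age, "birth weight and other characters that are different in two groups after initial analysis".

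Three other places bear on what this rule can admit:

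- Randomization: infants in the cell group "will receive an infusion of ACBMNC within 24 h after birth".
- Basic Clinical Data Collection: item (4) includes "postnatal steroid use, surgical closure of patent ductus arteriosus, and use of blood products". Table 2 records all three at the intervention visit and again at 36 weeks of postmenstrual age.
- Background: in the group's earlier study, "ACBMNC infusion resulted in a significant decrease in the duration of mechanical ventilation (3.2 vs. 6.41 days" in the two groups.

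On centres, the Statistical Analysis section says: "The Breslow-Day test and Corchran-Mental-Haenszel (CMH) test will be used to adjust the data derived from different participating centers". The same section also provides for an unadjusted chi-squared comparison.

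**The concern.** Randomisation protects the comparison only when the covariates could not have been influenced by treatment. The rule names events next to baseline characteristics, sets no time limit, and leaves the list open to whatever is found to differ between the groups. With infusion in the first day, most postnatal events come after it. The requirement that a covariate be known to affect BPD gives no protection, because a variable on the path from treatment to BPD meets it.

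If the infusion reduces, say, the need for steroids, and that in turn reduces BPD, then steroid use will tend to differ between the groups and so qualify for the model. Part of the real benefit is then credited to the covariate. At stake is the adjusted odds ratio for the primary outcome, which could understate a true effect.

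The second weakness is separate. Even when only baseline items are used, choosing them by observed imbalance means that nobody can write down the model before the data are seen.

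**Working it through.** **Inputs from the protocol.** Rates 60% and 35%, two-sided 5%, 80% power, and 140 infants in total, so 70 per arm (Sample Size). The protocol gives the rates for BPD; here they are applied to death or BPD.

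**The plan's own figure.** n = [0.6×0.4 + 0.35×0.65] × [(1.96 + 0.8416)/0.25]² = 0.4675 × 125.6 = 58.7, so 59 per group, as stated. At 70 per arm, power for 60% vs 35% is about 85%. The unadjusted odds ratio is (0.35/0.65)/(0.60/0.40) = 0.36.

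**Assumptions.** The document gives no event rates and no event-outcome odds ratios, so a range is used. Let T be treatment and M a binary post-infusion event with frequency m0 (control) and m1 (treated):

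logit P(outcome) = a + t·T + ln(OR_M)·M

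The constants a and t are solved so that the overall rates stay at 60% and 35%. exp(t) is the odds ratio that a model containing M estimates. Power comes from 3,000 simulated trials per row, 70 per arm, Wald test at 5%.

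| Event, control vs treated | Event-outcome OR | Treatment OR with event in model | Power without event | Power with event |
|---|---|---|---|---|
| 60% vs 50% | 4 | 0.37 | 85% | 77% |
| 60% vs 45% | 4 | 0.40 | 85% | 72% |
| 60% vs 40% | 4 | 0.43 | 86% | 63% |
| 60% vs 40% | 8 | 0.44 | 85% | 57% |
| 60% vs 35% | 8 | 0.50 | 85% | 41% |

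**Last row by hand.** Outcome risks without and with the event are 31.8% and 78.8% in controls (0.4×0.318 + 0.6×0.788 = 0.60), and 18.8% and 65.0% in treated infants (0.65×0.188 + 0.35×0.650 = 0.35). Among infants with the event, the odds ratio is (0.65/0.35)/(0.788/0.212) = 1.857/3.717 = 0.50.

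**Why power falls in the first row although the odds ratio hardly moves.** Conditioning on a prognostic variable that treatment does *not* affect moves an odds ratio away from 1. With the event at 60% in both arms and event-outcome OR 4, the risks are 40.4% and 73.1% in controls and 17.8% and 46.5% in treated infants. Without the event this gives (0.178/0.822)/(0.404/0.596) = 0.32. Against that reference, 0.37 is already attenuated.

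**Chance that the rule selects the event.** The plan does not define *different*; take p < 0.05. For 60% vs 35%: z = 0.25/√(0.4675/70) = 3.06, and Φ(3.06 − 1.96) = 0.86. For 60% vs 50%: z = 0.10/√(0.49/70) = 1.20, and Φ(1.20 − 1.96) = 0.22. An event that treatment does not affect would be picked about 5% of the time.

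**Imbalance selection among true baseline covariates.** With k independent candidates, the chance that at least one differs at p < 0.05 is 1 − 0.95^k: 23% for 5, 40% for 10, 64% for 20. In 4,000 null trials per setting (5 or 10 candidates, 70 per arm), the selected model rejected in about 4.8%, against 5.1% unadjusted. Counting a success when either model was significant gave 5.4%–5.6%.

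**The case against.** The strongest reply is that the rule does not prescribe adjustment for steroids, duct surgery or blood products. The bracket opens with i.e., names two baseline variables, and continues with *characters*. Basic Clinical Data Collection uses *characteristics* for sex, gestational age, birth weight, delivery mode and Apgar score, and places steroids, duct surgery and blood products under routine interventions. A careful analyst could therefore read the rule as baseline-only. This stands as a fair reading. It does not close the matter, because "baseline characteristics and events known to affect the occurrence of BPD" names events expressly and no other section excludes later ones.

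Four stronger inferences are tempting, and the document does not support them:

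- *The rule picks a variable exactly when treatment has changed it.* Chance imbalance also triggers selection. A treatment effect only makes selection more likely.
- *The loss of power is known and severe.* It rests wholly on assumed rates and associations. The table's losses apply when the event is in the model. Under the rule it enters only in some trials, so the average loss would be smaller.
- *Type I error is inflated because a chi-squared test, a logistic model and a CMH test are all used.* That requires success to be claimed on any of the three, which the section does not say.
- *The randomised contrast is lost.* The unadjusted chi-squared comparison remains in the plan.

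**Conclusion.** The concern holds in this form: the covariate rule permits adjustment for variables that the infusion may have altered, and it fixes the final model only after the groups have been compared. The rule is stated in the protocol article and badly drawn; it is not a detail left to another document.

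Under the assumptions shown, the odds ratio moves from 0.36 to about 0.37–0.50, and power falls from about 85% to about 77%–41% when such an event is in the model. The lower end is a modest cost and the upper end a serious one. The protocol offers nothing to choose between them, beyond its own report that the same treatment shortened ventilation. These figures use 70 per arm. The Abstract and the Study Design section give 200 infants, which at 100 per arm would start from about 95% power; the attenuation of the odds ratio does not depend on the number of infants.

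Choosing true baseline covariates by imbalance is a weakness of pre-specification. It is not a demonstrated source of false-positive results.

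A minor wording point: the Breslow-Day test examines whether the odds ratio is the same across centres and does not adjust for centre. The CMH test does.

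**What to change.** In the Statistical Analysis section:

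1. Delete *events* and the clause that admits characters found to differ after an initial analysis.
2. Name one primary analysis of death or BPD in all randomised infants, with a closed list of pre-randomisation covariates: gestational age, birth weight, and centre as a random effect or a stratum. Either handling of centre is acceptable if it is fixed in advance.
3. Label the remaining tests of the primary outcome as sensitivity analyses.
4. Label any model that contains post-randomisation variables as exploratory.
5. Reword the centre sentence so that CMH is the adjustment and Breslow-Day a check of homogeneity.

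The cost is wording only. Gestational age and birth weight are already collected, centre is known for every infant, and no new data are needed.
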